### Research questions 2 and 3: context and potential moderators

#### Context

A detailed situation analysis at state and local government levels was carried out in each state during design of the intervention. This will be reviewed and summarised with respect to potential contextual factors that could affect the implementation. In addition, each quarter, as part of the facility case study, personnel document any environmental factors that they feel may have influenced implementation or outcomes of the programme. Both the situation analysis and facility case study borrow extensively from the work carried out in the PRIME programme,^54^ which shared many contextual characteristics with mhSUN. The importance of these contextual factors will be further explored by key informant interviews, recognising that this is a dynamic process, with the programme being affected by, and affecting, the local environment.

#### Moderators

Postulated moderators for effective implementation were derived from theoretical frameworks and the ToC developed for this project. This process drew upon local experience to highlight what factors might influence outcomes. These were documented as preconditions for achieving the different steps of change in the mhSUN ToC (and associated indicators assigned to them) (see previous mhSUN publication^19^):
Participant responsiveness/satisfaction: Does quality of treatment or staff clinician behaviour influence service use patterns?Resources: What was the effect of availability/lack of availability of human resources, health information systems, medication, clinic infrastructure and other resources to implementation of the programme as per time/output expectations?Recruitment/service uptake: What factors increased service use and the number of appointments patients attended? What was the effect of recognised barriers to access (costs, distance) and of the awareness programme?Model description and communication: Did staff feel they understood the model and feel involved in its development and adaptation? How do base training and refresher sessions improve staff knowledge and improve treatment?

Information on putative moderating factors influencing implementation have also been included in data to be collected (Table 3).

**Table 3 tab03:** Potential moderating factors and data sources

Potential moderating factors	Data source^a^
Participant responsiveness/satisfaction	
Experience of service	Cohort questionnaire (PACIC)
Participant experience	Qualitative interviews with patients and staff
Quality of clinical care	Supervision reports
Resources	
Availability of medication	Facility case study Q6
Availability of key staff at clinic	Facility case study Q4
Integration of mental health into health information system	Facility case study Q1c
Condition and availability of private clinic room	Facility case study
Recruitment/service uptake	
Cost of service	Cohort questionnaire (CSRI)
Socioeconomic status	Cohort questionnaire (HES Nigeria)
Distance from facility	Cohort questionnaire (patient records)
Timing of awareness programme	Awareness programme log book/service use data/HMIS
Model description	
Training provision	Training logs (basic and refresher training)
Training outcomes	Pre- and post-training questionnaires
Service provider understanding of model	Qualitative interviews with service providers

a. See supplementary material for facility case study and cohort questionnaire details.

PACIC, Patient Assessment of Chronic Illness Care; CSRI, Client Service Receipt Inventory; HES Nigeria, Household Expenditure Survey; HMIS, (routine) health management information system at Primary Health Care.

We will use descriptive analysis of facility-level data and logs (training attendance, medication availability, staff presence, etc.), using data at different time periods to compare outcome with and without the relevant moderating factors of impact of awareness-raising programme on service uptake; availability (or not) of medication, and any correlation with service provision and uptake; and actual rate of programme components bedding down (compared with initial plans and expectations).

In addition, as the programme is being carried out in two states (and within seven and eight districts within each of these), we will be able to examine the effect of differences in implementation across location; for example, the impact of localised policies on drug distribution on availability, the effects of support from local political and health leadership, and the influence of insecurity on implementation in different districts.

For data collected through the cohort questionnaire, we will be able to summarise data on costs, service use and other cross-sectional information, and carry out logistic regression analyses (using Stata for Windows version 9 to generate odds ratios) to identify associations between different factors and outcomes, such as looking at whether a group reporting easy versus barriers to access to a clinic had better outcomes.^55^ Although such analysis risks being underpowered, we will explore whether the results confirm or refute our hypotheses, and we will be triangulating this with the qualitative work, allowing us to explore potential mechanisms, using the experience and expertise of key informants.

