A situation analysis carried out at the programme development stage.A facility case study comprising quarterly evaluation of facilities, including a facility checklist of human resource presence, medication availability and infrastructure, as well as record of changing context.Log books of intervention elements such as governance processes, advocacy meetings, awareness campaign, training and supervision.Routine health information system recording service use statistics, disaggregated by primary diagnosis and gender, and patient clinical records.Supervision record forms documenting monthly supervision visits, incorporating assessment of quality of care provided.Cohort of patients comprising a sample of patients with each of the three major diagnoses of epilepsy, psychosis and depression (the priority conditions for the service) will be interviewed on entry to the service and at 6 months. Data includes validated questionnaires on clinical, human rights and disability outcomes, patient satisfaction and service use (including costs). A conservative sample size of 200 participants per diagnosis has been calculated to achieve sufficient power to measure change in outcomes on clinical and disability measures. This was based on outcomes of similar studies exploring integration of treatment of depression, psychosis and epilepsy in primary care in LMIC settings.^42,43^Qualitative data collected through in-depth key informant interviews, and observation notes kept during site visits. Processes to engage and gain buy-in from relevant actors are built into the governance of mhSUN, so we expect to be able to obtain consent from key actors.

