### Research question 4: accessibility and acceptability

Ensuring accessibility and acceptability was a consideration throughout the design of the intervention, as demonstrated by the use of ToC and extensive engagement with local authorities. Language and cultural understanding are a consideration throughout in the research and programme elements, as shown by awareness-raising and local concepts of mental illness being incorporated into communication materials. Accessibility and acceptability will be assessed through the cohort questionnaire (PACIC), and in qualitative interviews with patients, carers and healthcare staff, drawing on similar research.^56^ Focus group discussions will be used both in qualitative evaluation of acceptability of the intervention, and in triangulating with factors deemed to influence outcomes, as acceptability is a potential moderator (part of Participant Responsiveness (see Fig. 1).

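### Cost, distance and socioeconomic status are listed as uptake moderators but measured only in people who entered the service, so their effect on first entry cannot be estimated and the barrier-outcome comparison applies to attenders only

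*Protocol article*

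**What the plan says.** All places are in the protocol article.

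- **Who is in the cohort** (Methods, data sources and analysis). Patients with epilepsy, psychosis or depression, 200 per diagnosis, who "will be interviewed on entry to the service and at 6 months".
- **The question** (Moderators, recruitment/service uptake item). It has two parts: "What factors increased service use and the number of appointments patients attended" and "What was the effect of recognised barriers to access (costs, distance) and of the awareness programme".
- **The data sources** (Table 3, same heading). Cost is assigned to "Cohort questionnaire (CSRI"), socioeconomic status to the household expenditure items of the same questionnaire, and distance to the cohort questionnaire with patient records. Only the timing of the awareness programme is assigned to log books and routine service-use data.
- **The analysis** (Moderators, last paragraph). Logistic regression in the cohort to relate factors to outcomes, "such as looking at whether a group reporting easy versus barriers to access to a clinic had better outcomes". The caveat given is low power, with triangulation against the qualitative work.
- **Accessibility** (Research question 4). "Accessibility and acceptability will be assessed through the cohort questionnaire (PACIC") and through qualitative work with patients, carers and staff. Table 1 sends the distance and cost parts of this question back to the moderator analysis.

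**The concern.** Everyone in the cohort has taken the step whose determinants are being asked about. First entry does not vary among them, so nothing in the cohort can be associated with it, whatever the model or the sample size. An analysis plan cannot repair this, because the mismatch lies in the article's own pairing of question and source.

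A second problem follows. People who attend despite a barrier may differ from those who attend without one, for example in severity. If so, a comparison of their outcomes mixes any effect of the barrier with the effect of who got through it.

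The results are meant to inform investment and policy decisions by health authorities (Ethics and dissemination). Little difference by distance or cost among attenders could be read as evidence that access is adequate, when the people deterred were never observed.

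**Working it through.** **1. Does another described source close the gap?**

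- *Equity* (Coverage/reach): service-use data split by socioeconomic status and distance, among other factors. These cover users only.
- *Contact coverage* (Coverage/reach): this has a population denominator, published prevalence weighted for local demographics. It is not tied to cost, distance or socioeconomic status.
- *Access interviews and focus groups* (Table 1; Research question 4): patients, carers and staff. The key informants for research question 1 include community leaders, who could speak about non-users only at second hand.
- *Comparisons across districts and time periods* (Moderators): these concern drug supply, leadership support, insecurity and the awareness programme, not individual cost, distance or socioeconomic status.

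None of them gives these three factors for people in need who did not attend.

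**2. What the cohort can say about entry.** Let s be the share of attenders with a barrier and p the share of people in need with that barrier. The ratio of uptake, barrier versus none, is

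(s / p) / [(1 − s) / (1 − p)].

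The cohort gives s; no described source gives p. Assume s = 0.30:

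| p (assumed) | Calculation | Uptake ratio |
|---|---|---|
| 0.15 | (0.30/0.15) / (0.70/0.85) | 2.43 |
| 0.30 | (0.30/0.30) / (0.70/0.70) | 1.00 |
| 0.50 | (0.30/0.50) / (0.70/0.50) | 0.43 |
| 0.70 | (0.30/0.70) / (0.70/0.30) | 0.18 |

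Identical cohort data fit a barrier that appears to raise uptake, does nothing, or cuts it by four-fifths.

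**3. What selection could do to the barrier-outcome odds ratio.** Assumed model: barrier B in half the population and an independent factor U ~ N(0,1), such as severity.

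- Attendance: logit P(attend) = a + bB + uU
- Recovery: logit P(recover) = yU, so the true odds ratio for B is 1.00

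Among attenders with barrier status B, the recovery probability is E[P(attend) × P(recover)] / E[P(attend)], averaged over U. The odds ratio compares B = 1 with B = 0. By numerical integration:

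| a | b | u | y | Attend, no barrier / barrier | Odds ratio among attenders |
|---|---|---|---|---|---|
| −2 | −1 | 1 | −1 | 0.155 / 0.069 | 0.91 |
| −2 | −2 | 1 | −1 | 0.155 / 0.028 | 0.86 |
| −2 | −2 | 1 | +1 | 0.155 / 0.028 | 1.16 |
| 0 | −2 | 1 | −1 | 0.500 / 0.155 | 0.75 |
| 0 | −2 | 1 | +1 | 0.500 / 0.155 | 1.33 |

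Over b from −1 to −2, u from 0.5 to 1 and y from −1 to +1, the range is 0.75 to 1.33. A simulation of the same setting gave 0.76 to 1.35; the difference is Monte Carlo error. With b = 0 or u = 0 the odds ratio is 1.00. In this model B has no effect once U is held fixed, so adjusting for U restores 1.00. A real severity score measures U imperfectly and would remove only part of the distortion.

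**4. Scale against sampling error.** Assume all 600 patients (3 × 200) split 300/300 by barrier, with recovery near 50%. The standard error of the log odds ratio is about √(4/300 + 4/300) = 0.163. An observed 0.89 would then have a 95% interval of about 0.65 to 1.23.

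The article's 200 per diagnosis cannot be reproduced, since no effect size, power or dropout is given. Nothing here depends on it.

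**The case against.** Four points can be made for the plan.

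*Uptake is wider than first entry.* The article's question also covers service use and number of appointments. Both vary among entrants, and the cohort collects service use. This stands. A reader might infer that the cohort says nothing about uptake, but the limit applies to first entry only.

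*The regression of outcome on access barriers is one example and a legitimate aim.* It is introduced as an illustration, and research question 2 in Table 1 asks for outcomes with and without each moderator. This stands, so the analysis should not be dropped as a stand-in for another question.

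*Selection bias is not demonstrated.* A reader might infer that the comparison is biased, and towards worse outcomes for people facing barriers. The documents do not support that. Bias requires both the barrier and another cause of recovery to affect attendance; its sign depends on how that cause acts, and the association remains a valid description of attenders. Distortion of the size most easily imagined would also lie within sampling error (step 4), in an analysis the article already treats as possibly underpowered. But the low-power caveat does not cover selection, which more patients would not cure.

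*Research question 4 asks about patients, carers and staff.* A reader might infer that its conclusions would be wrong for non-users, but it makes no claim about them. What remains is that its cost and distance parts pass to the moderator analysis, where the limit applies.

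None of this supplies cost, distance or socioeconomic status for people who never entered, and the limitations section does not mention their absence.

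**Conclusion.** The point holds in a limited form. From the sources described, the effect of cost, distance and socioeconomic status on first entry to the service cannot be estimated. That follows from recruitment at entry and needs no numerical assumption; the 2.43 to 0.18 range only illustrates it, for an assumed 30% of attenders with a barrier.

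The comparison of outcomes by ease of access applies to attenders and may be distorted by selection if barriers and severity both affect attendance. Its direction and size are unknown. The odds ratios of 0.75 to 1.33 rest wholly on assumed inputs and show what is possible, not what is expected.

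The design can still support conclusions about continued use and outcomes among entrants. The text should be corrected because it changes what a null result may be taken to mean; it does not invalidate the evaluation.

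**What to change.** 1. **Table 3 and the Moderators analysis paragraph.** State that the cohort analyses of cost, distance and socioeconomic status concern continued use (number of appointments, retention at 6 months) and outcomes among people who entered. Add that a null result is not evidence that these barriers leave uptake unaffected.
2. **Barrier-outcome regression.** Keep it, adjust it for the Clinical Global Impression-Severity score at entry, which the Coverage/reach section says is used for all cohort participants, and report it as an association among attenders.
3. **Strengths and limitations.** List the absence of non-users from the cohort, interviews and focus groups. The planned focus groups cannot fill the gap, since none is described as including non-users.
4. **Only if catchment denominators already exist,** add contact coverage by distance band or area. The documents describe none at that level, so this should not be promised otherwise.

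The cost is a narrower claim, some rewording and a little more analysis. Items 1 to 3 need no new enrolment and no new data collection.

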Data collection is carried out by research assistants and managed by a research coordinator in each site. The research team is attached to the Federal Neuropsychiatric Hospital where the mhSUN programme is managed, but functions independently of the implementing teams in terms of roles. Data collection forms were developed and tested for the facility data, supervision records and log books for activities. Mental health elements also had to be incorporated into the routine Primary Health Care data collection forms. as this was not previously included. The cohort questionnaire is programmed into a mobile application (Mobenzi Android v4.15.0; www.mobenzi.com), allowing efficient and secure data collection, storage and transfer. Such applications have the advantage of flexible use of skips and assured completion of questions, making data collection efficient, reducing missing data and increasing data quality.

We now outline background, methods and analysis for each research question in greater detail.

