### Primary research question 1: intervention, adherence (fidelity, dose) and coverage

The intervention has been described, after development with ToC, including its essential components and the theoretical underpinning of these components.^19^ The major components of the model, as described in the Operations Manual, are summarised in Table 2. This is used as a basis for training and is available to implementers, and it is against this that fidelity will be measured.

**Table 2 tab02:** Components of the mhSUN intervention, and data sources for assessment of fidelity

Component (documented in mhSUN Operations Manual)	Expected interventions	Source of data for assessment
1. The policy and legislative framework for service reform	Alignment to policy in project development Engagement with political/health leaders	Operations Manual Activity log books
2. The structure and management of the service, governance	Establishment of Steering Committee and 6 monthly meetings Monthly programme meetings	Activity log books Meeting participant lists
3. Equity and access to the service	Community awareness programme	Health information system (disaggregated data)
4. Human resources and capacity building	Identification of personnel Core mhGAP training 6-monthly refresher training	Training records Facility checklist
5. Supervision and maintaining quality of care	Supervisor training Monthly supervision from federal hospital each month	Supervision forms
6. Clinical contact and referrals	Identification of clinic space Availability of trained personnel Links to referral hospitals	Facility checklist
7. Maintaining contact, strategies to deal with non-attenders	Community champions	Patient clinical records Health information system
8. Availability of medication	Advocacy and engagement with state on drug supply chain	Facility checklist Facility case study Drug Revolving Fund records (Calabar)
9. Raising awareness, and increasing uptake of the service	Community awareness programme Community champions	Activity log books Health information system
10. Record-keeping and health information system	Development and use of mental health information system	Health information system
11. Social integration and rehabilitation	Link to community champion Community awareness programme	Patient clinical records

mhSUN, Mental Health Scale Up Nigeria.

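### The period comparison planned for the awareness programme cannot separate a campaign effect from background change in a new service with new recording

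*Protocol article*

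**What the plan says.** The Moderators section asks a question in terms of effect: "What was the effect of recognised barriers to access (costs, distance) and of the awareness programme". Table 1 words research question 2 the same way and lists comparison with and without the factor of interest, alongside logistic regression.

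For facility-level data and logs the method is descriptive, "using data at different time periods to compare outcome with and without the relevant moderating factors of impact of awareness-raising programme on service uptake". The same sentence adds two further items: "availability (or not) of medication, and any correlation with service provision and uptake", and the "actual rate of programme components bedding down (compared with initial plans and expectations". The third is an output in its own right, set against the plan. It is not described as an adjustment to the other two.

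Table 3 gives the source for campaign timing as "Awareness programme log book/service use data/HMIS". On recording, Methods, data sources and analysis says "Mental health elements also had to be incorporated into the routine Primary Health Care data collection forms", because they had not been there before. Table 2 shows what else the programme delivers: core training, "6-monthly refresher training", monthly supervision, community champions and engagement with the state on drug supply. The article also says "we will be able to examine the effect of differences in implementation across location", over two states with seven and eight districts. Its examples are drug distribution policy, leadership support and insecurity.

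**The concern.** If uptake is moving for any other reason, a comparison of periods with and without the campaign takes in that movement as well. The article itself gives three reasons to expect movement:

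- the service is being established;
- the recording system is being established with it, so counted attendances can change while true attendances do not;
- other components meant to raise or sustain uptake operate over the same period.

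The method is called descriptive, but the question put to it is about effect. The article also says the results are meant to inform investment and policy decisions by health authorities. A rising background could make an inert campaign look useful, and a falling one could hide a useful campaign. Medication availability has a related problem: stock can come and go, so its overlap with calendar time can push the association in either direction.

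**Working it through.** The article states no figure for this comparison, so there is nothing to reproduce. The check asks how far a plain period contrast can move when the campaign does nothing. **All growth rates, durations and starting counts below are assumptions, not figures from the documents.**

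**1. Adjacent six-month periods.** Let expected monthly uptake grow by a factor (1+g) each month, with no campaign effect. Each month in the second period is (1+g)^6 times the matching month in the first, so the after/before ratio is (1+g)^6.

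- g = 0: 1.00
- g = 2%: 1.02^6 = 1.126
- g = 5%: 1.05^6 = 1.340
- g = 10%: 1.10^6 = 1.772

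The direction reverses if uptake is falling. At −2% per month, 0.98^6 = 0.886.

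**2. Adjacent twelve-month periods.** The ratio becomes (1+g)^12: 1.13 at 1%, 1.27 at 2% and 1.80 at 5%. Longer windows make the contrast worse.

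**3. Does a time term help?** Poisson counts were simulated for one series of 24 months, starting from 20 visits per month, with the campaign beginning at mid-period (1,000 runs per setting). The crude ratio was compared with a Poisson regression containing a linear time term and a campaign step.

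| Growth per month | True campaign ratio | Crude ratio (median) | Trend-adjusted ratio (median) | Share of runs with p < 0.05 (adjusted) |
|---|---|---|---|---|
| 0% | 1.00 | 1.00 | 1.00 | 5.3% |
| 2% | 1.00 | 1.26 | 1.00 | 4.9% |
| 5% | 1.00 | 1.80 | 1.00 | 4.2% |
| 0% | 1.30 | 1.30 | 1.30 | 36.4% |
| 2% | 1.30 | 1.64 | 1.30 | 42.2% |
| 5% | 1.30 | 2.34 | 1.30 | 55.2% |

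The time term removes the distortion when the trend is of the form modelled. The last column shows the price: one series of this size detects a true ratio of 1.30 only about four to five times in ten.

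**4. Medication availability.** Take the same 24 months with no true effect, and compare months in stock with months out of stock, at 2% and 5% growth:

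- in stock only in the later half: (1+g)^12 = 1.27 and 1.80;
- in stock only in the earlier half: 1/(1+g)^12 = 0.79 and 0.56;
- alternating quarters, starting in stock: 1/(1+g)^3 = 0.94 and 0.86.

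The sign depends entirely on when stock was present.

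**The case against.** The strongest reply has four parts.

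- **The analysis is descriptive and will not be read alone.** Bedding down is tracked, staff record contextual influences each quarter, integration of mental health into the information system is itself a listed moderator, and results are triangulated with interviews. This stands against any claim that a rise in uptake *will* be credited to the campaign. A reader might infer that, but the article commits to no such conclusion. The safeguards can temper interpretation, but they cannot subtract a trend from counts.
- **Growth is not established.** The article describes a fragile system with political uncertainty and communal violence, where uptake could stall or fall. It gives no campaign dates, and the awareness programme is a core component that may have started with the service or recurred. This stands: the ratios above are illustrations, and a clean period before the campaign may not exist.
- **This is a condensed article.** Model detail may sit in a fuller document. That would answer a complaint about unspecified terms. It does not answer the point that the comparison stated here is a period contrast put to a question about effect.
- **It is not the only quantitative work on moderators.** Logistic regression on the cohort and comparison across locations are also planned. This stands, although neither is described as using campaign timing.

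A reader might also infer that medication and uptake will be correlated within the same quarter, and that high attendance uses up stock. The article says neither; it leaves the form of the correlation open.

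**Conclusion.** The point holds in a limited form. The stated comparison for the awareness programme names no allowance for an underlying trend, in a service where both delivery and recording are new and other components run alongside. It cannot separate a campaign effect from background change. Whether bias will arise, how large it will be and in which direction cannot be learned from the documents. The six-month ratios of 1.13, 1.34 and 1.77 rest wholly on assumed constant growth of 2%, 5% and 10% per month and a null campaign; with no growth there is no distortion. For medication the same weakness exists without a predictable sign. This concerns a secondary question and the reading of a descriptive analysis, so it is worth correcting but does not threaten the evaluation as a whole.

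**What to change.** State the following in the plan.

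1. Plot routine uptake counts, at whatever reporting interval exists, against each district's logged campaign dates. The article does not say that counts are monthly.
2. Where there are enough points before the campaign, fit a count model with district effects, an underlying time trend and a change at the campaign date. Use any differences in timing among the 15 districts as a concurrent comparison.
3. Where campaigns began with the service, or all began together, report before/after figures as temporal association only and say that campaign and time cannot be separated.
4. For medication, relate availability to uptake within facility, with the same time term. A lagged comparison is optional.

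The cost is a little more analysis of sources the article already lists, and wider, possibly smaller, effect estimates. The model also relies on the trend being reasonably described by its time term. With few early points that cannot be checked, and item 3 then applies.
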